#### Eligibility criteria

People with any type of diagnosed or suspected acquired brain injury who meet the study inclusion criteria are eligible to participate (Table 1).

**Table 1 Tab1:** Eligibility criteria for HOPE4ABI

Inclusion criteria	Exclusion criteria
• Age ≥ 18 years, UK-based • Diagnosed ABI (including head injury, stroke, meningitis, brain tumour, encephalitis, hydrocephalus, cerebral abscess, anoxic brain injury, carbon monoxide poisoning, encephalopathy, cerebral oedema, compression of the brain) ≥ 3 months prior to trial entry, category B/C/D on Patient Categorisation Tool [43, 44] ◦ OR suspected ABI, with corresponding self-reported history of brain injury, behavioural, psychological, physical, or emotional difficulties (reported at self-referral / research nurse screening phase), ≥ 3 months prior to trial entry • Capacity to give informed consent • Ability to communicate in English to participate in the intervention and complete outcome measures • Internet connection and an Internet-enabled device	• Self-reported severe mental illness (e.g. schizophrenia) • Diagnosis of dementia or other neurodegenerative disorder • Drug- or alcohol-dependency • Actively suicidal or attempted suicide in the last 3 months

#### Participant identification, recruitment and informed consent

Participants are referred to the trial through three routes: (i) self-referral, (ii) organisation referral and (iii) NHS referral, as outlined below.

#### Self-referrals

The trial will be advertised via multiple routes including social media (e.g. Facebook, Twitter), partnering organizations’ websites, newsletters and events, and the NIHR ‘Be Part of Research’ network. People with ABI may be exposed to these adverts through deliberate search (e.g. via ‘Be Part of Research’) or simply through newsfeeds on their social media channels.

#### Organisation referrals

Many partnering organisations (e.g. Headway, Brainstrust) have existing groups of research volunteers who are themselves living with brain injury. Partner organisations may distribute our trial adverts amongst their own networks of volunteers via email, social media, newsletters, meetings or events, in a more targeted approach than the self-referral described above.

#### NHS referrals

Participant Identification Centres (PICs) will identify eligible patients and refer them to the study website. Two trusts will initially act as PICs: University Hospitals Coventry and Warwickshire NHS Trust, and Torbay and South Devon NHS Foundation Trust. Further Trusts may be added as the study progresses (e.g. if participant recruitment rate is slow). Patients attending relevant outpatient neurology/stroke/TBI clinics will be screened against the eligibility criteria using a combination of medical notes and consultation with the clinical team. The anonymized screening log (see Fig. 1) will be completed by the clinical team and returned to the research team on a weekly basis.

**Fig. 1 Fig1:**
[figure not shown]
Example screening log to be completed by the clinical team at the PIC site

In all referral routes, participants will receive information via a study advert/leaflet, containing a link/QR code to access the study website. The participants’ route through the study is summarised in Fig. 2.

**Fig. 2 Fig2:**
[figure not shown]
Study flow chart

After providing informed consent, and approximately 1 week before the course start date, participants complete the baseline questionnaires and are randomised to the peer-supported HOPE4ABI course (intervention group; IG) or the self-directed HOPE4ABI course (control group; CG). A subset of participants from each trial arm will be randomly selected to take part in post-course acceptability interviews. Participants who completed all or most of the intervention, as well as those who completed fewer than half of the sessions (including those who dropped out) will be interviewed to assess the acceptability of the intervention and trial procedures.

#### Randomisation, allocation concealment and blinding

The participants will be randomly assigned to the IG or CG using a 1:1 allocation ratio. Randomisation is initiated automatically on completion of the baseline questionnaires. Participants will be notified of their allocated group (IG or CG) via email, along with a weblink to join the relevant course. It will not be possible to blind participants to allocation past the point of randomisation, due to the notable differences in the intervention delivery between the IG and CG (i.e., peer-supported, or self-directed). Analysis of quantitative outcome measures will be conducted by a researcher who is blinded to allocation.

#### Interventions

HOPE4ABI will provide digital self-management support for psychological and sexual wellbeing issues that are common across different types of brain injury [10, 11]. HOPE4ABI is a novel offering, compiled of repurposed elements of an existing self-management intervention—The HOPE Programme©—alongside bespoke, co-designed sexual wellbeing support. HOPE stands for ‘Help to Overcome Problems Effectively’, and The HOPE Programme© is built on the principles of positive psychology, cognitive behaviour therapy, acceptance commitment therapy and mindfulness. It has a unique focus on hope and gratitude to create an upward spiral of positivity [45] and embeds group curative factors, such as instilling hope, universality and altruism [46], to support self-management of health and wellbeing of long-term conditions.

HOPE4ABI is an 8-week, asynchronous digital self-management programme that has been co-designed with and for people with ABI. Following a series of co-creation workshops with people affected by brain injury, common themes were identified regarding gaps in care and unmet self-management needs. Each theme is addressed across the 8-week intervention, through curated content including videos, educational content, activities, homework suggestions and additional resources (Table 2). Bespoke videos, quotes and podcasts are included featuring professionals, researchers and people living with ABI.

**Table 2 Tab2:** Topics covered within each weekly module of HOPE4ABI

Session	Indicative content topics
Week 1: Instilling hope	• Introduction to self-management • The power of gratitude • Practicing self-compassion • SMARTER^a^ goal setting • *Forum/journal prompt*: reasons for joining the course
Week 2: Living with ABI	• Effects of ABI on multiple aspects of health and wellbeing • Overview of common issues caused by ABI • Talking to others about ABI • Preparing for appointments with health professionals • *Forum/journal prompt*: what are your priorities right now? What do you want to change?
Week 3: Communication	• Staying connected with others • Accepting help • Starting and managing difficult conversations • Forming deeper connections
Week 4: Sex and relationships	• Sexuality, intimacy and relationships after ABI • Embracing new norms • Understanding the needs of others • Sexual expression • New connections and dating
Week 5: Physical health	• Managing fatigue • Sleeping well • Staying active with ABI • Prioritising, planning and pacing
Week 6: Cognitive and mental wellbeing	• Understanding stress • Managing frustration • Low mood and worries • Recognising impulsivity • Brain fog—tips and tricks
Week 7: Emotional wellbeing	• Challenging unhelpful thinking styles • Building confidence and self-esteem • Mindful emotions • Self-compassion and caring for others • Reframing negative thoughts
Week 8: Living with hope	• Knowing your strengths • Happiness and hope • Building resilience • Planning meaningful activities

^a^*SMARTER* SMARTER is an acronym used by many organisations for goal setting and stands for Specific, Measurable, Achievable, Relevant, Time-bound, Enjoyable and Reward

The peer-supported HOPE4ABI course uses forums and messaging facilities that act as a conduit for communication between participants, peers and facilitators. The self-directed HOPE4ABI course contains all the same material but does not include peer support or interaction with other participants. In place of discussions, the self-directed course has a journal option for recording thoughts and making notes.

#### Safety

The peer-supported HOPE4ABI course is moderated by trained peer facilitators with lived experience of ABI. Facilitators are trained in both health coaching (provided by a QISMET accredited trainer) and sexual wellbeing coaching (provided in collaboration with The Stroke Association) and are scored by a QISMET accredited trainer throughout the course against checklists to monitor fidelity of delivery.

Mental and sexual wellbeing can be sensitive issues so participants can decide how much to engage with topics in the course. Participants who feel any emotional or psychological distress at any time can leave the activity or withdraw from the research entirely. They are advised to discuss any sexual or psychological wellbeing concerns with a professional by contacting their GP or NHS 111. If the research team suspects a participant may be at risk of harm to themselves or others, we will advise them to contact their GP, NHS 111 or call 999 (in an emergency) for further support. We will contact the participant’s GP to inform them of their patient’s participation in the study and to alert them of any welfare concerns during the trial. We may also contact emergency services on the participants’ behalf if we feel there is an immediate risk to life.

Scores on mental wellbeing measures (see *Secondary Outcomes* section for full details) will be screened at T1 (8 weeks) and T2 (6 months) for any clinically meaningful *decrease* in scores since T0 (e.g. a *reduction* in Warwick Edinburgh Mental Well-being Score of 3 or more [47]). Responses to a brief measure of mental wellbeing [48] during the intervention phase (i.e. at weeks 1, 4 and 7) will also be monitored. Participants indicating a clinically meaningful decrease in WEMWBS will be contacted by the research team and encouraged to visit their GP. Participant distress during the intervention will be managed according to the study distress protocol.

### Primary outcomes

#### Referral and recruitment phase

The number of participants who were screened, eligible/referred, recruited and refused.

#### Intervention phase

The number of participants who enrolled in the course and accessed > 50% of the course content.

#### Post-intervention (months 2–6)

The number of participants who completed follow-up questionnaires, withdrawals, drop-outs/lost to follow-up, acceptability of interventions and trial process, and intervention usage data.

### Secondary outcomes

Scores on validated questionnaires will indicate changes pre- and post-HOPE4ABI on mental wellbeing, quality of life and sexual wellbeing (summarised below). Whilst changes cannot be determined with any statistical significance in this study, we assess the feasibility of administering this set of questionnaires with a particular focus on acceptability and participant burden. Participants receive a £10 gift voucher for completing follow-up questionnaires at each of the timepoints T1 and T2. The schedule of enrolment, intervention and outcome measures is summarised in Table 3.

**Table 3 Tab3:**
[figure not shown]
Summary of enrolment, interventions and assessments across the study period

#### Mental wellbeing

The Warwick Edinburgh Mental Wellbeing Scale (WEMWBS; [49]) is a scale of 14 positively worded feelings and thoughts, used to assess mental wellbeing within the adult population. The scale includes statements relating to experiences of positive affect, satisfying interpersonal relationships and positive functioning over the last 2 weeks. Participants rate each of the 14 items on a scale of 1 to 5, with a total positive mental wellbeing score ranging from 14 to 70, where higher scores represent greater positive mental wellbeing. A change in total score of ≥ 3 points is considered a clinically meaningful change [47].

The 7-item Short-WEMWBS (SWEMWBS [48]) will be embedded within the HOPE4ABI intervention in weeks 1, 4 and 7, so participants can monitor their own mental wellbeing throughout the course. This also allows researchers to monitor participants’ wellbeing and escalate any concerns promptly and appropriately (e.g. sudden decline in mental wellbeing score) in accordance with the study distress protocol.

#### Quality of life

Quality of Life after Brain Injury – Overall Scale (QOLIBRI-OS; [50, 51]) is a 6-item health-related quality of life measure (HRQoL) specifically tailored to patients with brain injury. QOLIBRI-OS is preferable to the full 37-item QOLIBRI [52] in this feasibility study, and since a global assessment of HRQoL is sufficient, interference from fatigue and cognitive impairment are reduced [53, 54] and participant response burden is low. Items related to satisfaction with physical, cognitive and emotional health, daily activities, social life and future prospects are scored on a 5-point scale: ‘Not at all’, ‘Slightly’, ‘Moderately’, ‘Quiet’ and ‘Very’. The total score is calculated by calculating the mean for the 6 items (provided no more than two responses are missing) and converting to a percentage by subtracting one and multiplying by 25. QOLIBRI-OS scores range from 0 to 100, with 100 being the optimal score indicating the best possible quality of life. A minimal clinically important change is a difference score of 12 [51]. QOLIBRI-OS is validated for TBI and stroke [51], meets standard psychometric criteria for reliability (Cronbach’s *α* = 0.86, test–retest reliability = 0.81) and has good construct validity in TBI populations [50].

#### Sexual wellbeing

Brain Injury Questionnaire of Sexuality (BIQS; [55]) asks participants to compare post-injury aspects of their sexuality with their pre-injury status on a 5-point Likert scale (1 = greatly decreased, to 5 = greatly increased). Fifteen questions cover changes in sexual functioning, relationship quality and self-esteem, and mood (reverse-scored). Scores across all items are summed, with higher total scores indicating more improvement. Additional questions that are not scored, provide insights such as relationship status and possible reasons for changes in sexual functioning, such as pain, fatigue and low confidence. Internal consistency (Cronbach’s *α* = 0.92), and convergent and divergent validity between the BIQS subscales and another established scale measuring sexual function [56] are good.

#### Sample size

For a feasibility trial, it is not necessary to conduct sample size calculations to power the study [57]. A randomised sample size of *n* = 60 (*n* = 30 per arm) was deemed appropriate for this feasibility study, informed by similar studies in this area [58] and National Institute of Health and Care Research (NIHR) guidelines [59]. If enrolment is < 50% (i.e. < 30 participants) halfway through the recruitment period (i.e. after 3 months), we will implement amendments to the recruitment strategy (e.g. recruiting more NHS referral sites and/or primary care settings, local and national brain injury charities and organisations). If the recruitment target is met < 3 months, the intervention period will commence ahead of schedule. For patients who have been recruited but are awaiting intervention commencement, we will send regular short updates about the study (e.g. ‘places are filling up fast’, ‘we look forward to meeting you’, ‘only 1 week to go’, etc.) via text, email, social media, etc., to maintain participant interest and prevent drop-out/attrition.

#### Data analysis

All quantitative data from the study will be analysed descriptively in concordance with the CONSORT extension for pilot and feasibility trials [60]. Sociodemographic and screening data representing the age, ethnicity and gender of all participants screened, referred or refused will be presented as proportions at the group level. This data may indicate trends in demographic groups that the HOPE4ABI study does or does not appeal to and inform future recruitment strategies to widen participation.

Measures of mean and variance, including confidence intervals and standard deviations, and number and percent for categorical variables, will be used to describe the full range of secondary outcome data (i.e. participant wellbeing questionnaire scores) at baseline and T1 and T2 follow-ups. All quantitative analyses will be performed using SPSS Statistics.

Qualitative data will be analysed by a combination of deductive and inductive thematic analysis [61], as appropriate. Interview transcripts will be read multiple times by two researchers and coded independently by each researcher. An inter-rater reliability score (Cohen κ) of < 0.70 [62] will indicate all data should be coded by a third researcher. The researchers will generate, review and refine themes and any sub-themes emerging from the data, for each of the IG and CG groups. Data derived from novel or spontaneous contributions to the interview by the participant (e.g. matter relating to acceptability not directly asked by the researcher) will be inductively coded. Qualitative data analysis may be supported using NVivo software.

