### Objectives

The primary objectives relate to assessing trial feasibility, via recruitment and refusal rates, retention and engagement rates for participation, and acceptability of trial procedures with a sample of participants and drop-outs for both arms of the trial. The secondary objectives will assess a preliminary signal of efficacy via pre-post change in scores on validated measures of mental wellbeing, quality of life and sexual wellbeing.

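### The secondary objective is pre-post change in scores, but the stated analysis summarises only the scores at each visit, so it gives no interval for the change

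*Protocol article*

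**What the plan says.** The Objectives section says that the secondary objectives assess "a preliminary signal of efficacy via pre-post change in scores on validated measures of mental wellbeing, quality of life and sexual wellbeing". The Secondary outcomes section repeats the aim: "Scores on validated questionnaires will indicate changes pre- and post-HOPE4ABI on mental wellbeing, quality of life and sexual wellbeing".

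Two instruments come with a threshold, and both thresholds are on the change scale. For WEMWBS: "A change in total score of ≥ 3 points is considered a clinically meaningful change". For QOLIBRI-OS: "A minimal clinically important change is a difference score of 12". No threshold is given for BIQS.

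The Data analysis section is the only analysis text for these outcomes. It makes the whole quantitative analysis descriptive: "All quantitative data from the study will be analysed descriptively in concordance with the CONSORT extension for pilot and feasibility trials". For the secondary outcomes the statistics are "Measures of mean and variance, including confidence intervals and standard deviations", with counts and percentages for categorical variables, and these "will be used to describe the full range of secondary outcome data (i.e. participant wellbeing questionnaire scores) at baseline and T1 and T2 follow-ups". It does not mention a change score, a spread of change or an interval for change, and it does not say which participants contribute at each visit.

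Two other sections bear on what is possible. Trial design and setting says that data from the different platforms are joined through one identifier per participant. Safety compares each participant's WEMWBS at T1 and T2 with their own T0 value, to detect a fall of 3 or more.

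**The concern.** The quantity named for analysis is the score at a visit. The quantity named in the objective is the change between visits. A confidence interval for the T0 mean and another for the T1 mean are each correct for their own purpose, but together they do not give an interval for the change. That interval also needs the correlation between visits, which is not among the stated outputs.

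Two things are at stake if the results section follows the text literally:

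- Readers looking for the preliminary signal will compare visit-wise intervals and may judge the change to be less precisely known than it is.
- The 3-point and 12-point thresholds, which are introduced to interpret change, have no stated use in the outcome analysis.

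This point concerns only how change is summarised. It does not address whether pre-post change is a good signal of efficacy in a two-arm trial.

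**Working it through.** The protocol states no SD, effect size or precision for the secondary outcomes, and the target of 60 is not based on a power calculation. There is therefore no figure of the plan's own to reproduce.

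**Inputs**

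- 30 per arm at T0 (Sample size section).
- 23 per arm at follow-up: 0.75 × 30 = 22.5, rounded up. The 75% is the retention cutoff in Transition to a definitive trial, borrowed here as an assumption. It is not a forecast.
- Equal SD at both visits, results in SD units, 95% level, normal multiplier 1.96 (assumptions; the protocol states no confidence level).
- Correlation ρ between visits: not given, so assumed 0.3, 0.5 and 0.7. The QOLIBRI-OS test-retest value of 0.81 (Quality of life section) serves as an upper value.

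**Precision of the mean change, per arm**

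Read from separate visit summaries, as if independent: 1.96 × √(1/30 + 1/23) = 1.96 × √0.0768 = 0.54 SD.

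Paired, on the 23 with both measurements: 1.96 × √(2(1 − ρ)/23).

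| ρ (assumed) | Paired half-width | Unpaired ÷ paired |
|---|---|---|
| 0 | 0.58 SD | 0.94 |
| 0.3 | 0.48 SD | 1.12 |
| 0.5 | 0.41 SD | 1.33 |
| 0.7 | 0.32 SD | 1.72 |
| 0.81 | 0.25 SD | 2.16 |

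The two readings are equal when 2(1 − ρ)/23 = 1/30 + 1/23, that is 1 − ρ = (23/30 + 1)/2 = 0.883, so ρ is about 0.12. Above that the unpaired reading is too wide; below it, it is not. With the arms actually randomised (27 and 26, Trial status section) the ratios agree to within 0.01.

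In WEMWBS points, at an assumed SD of 10 (range 8 to 12), the unpaired half-width is 5.4 points (4.3 to 6.5). The paired one at ρ = 0.5 is 4.1 points (3.3 to 4.9). Both exceed the 3-point threshold.

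**Shift in the difference of means through drop-out**

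Suppose the T0 mean uses everyone and the follow-up mean uses completers only. If nobody changes, the apparent change equals the completers' baseline mean minus the overall baseline mean. That is the fraction lost × the baseline gap between completers and drop-outs. With 25% lost:

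- gap 0.25 SD: 0.25 × 0.25 = 0.06 SD
- gap 0.5 SD: 0.25 × 0.5 = 0.125, about 0.13 SD
- gap 0.8 SD: 0.25 × 0.8 = 0.20 SD

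At an SD of 10 the middle case is about 1.3 WEMWBS points. The shift is zero if drop-out is unrelated to score, or if the same participants are summarised at each visit.

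**The case against.** The strongest reply is that the article is silent on this, not wrong. It never says that change will be obtained by subtracting unpaired means, that T0 covers everyone while T1 and T2 cover completers, or that change scores are excluded. Analysis sets and change tables often sit in a full protocol or SAP, and neither is shown. Much of this stands. A reader might infer that the visits are summarised on different people, that the planned intervals have the wrong precision, or that a drop-out bias is built in. The documents do not support any of these. Follow-up respondents are a subset of those randomised, no analysis set is stated, the visit-wise intervals are correct for visit means, and the shift needs both score-related loss and available-case means.

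A reader might also argue from how often an interval would exclude zero. That is a significance argument, and the protocol disclaims significance for these outcomes.

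It can further be said that on a common set of participants the difference in visit means equals the mean change, and that individual WEMWBS change is already computed for safety. Both are true. But no common set is named, the interval for change still cannot be obtained from the visit summaries, and the safety screen is not an outcome summary.

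The reply does not remove the core point. The article does specify the secondary analysis, down to the statistics and the times, and the quantity it chose is not the one in its objective. Keeping the analysis descriptive is no answer either, because a mean change with its SD and interval is itself descriptive.

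**Conclusion.** The point holds as a mismatch between objective and stated analysis: change is the aim, visit-wise scores are what is summarised, and no interval for change results.

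The numerical consequences are conditional. Reading change across visit summaries overstates the half-width by a factor of 1.12 to 1.72 for correlations of 0.3 to 0.7, and the overstatement disappears near a correlation of 0.12. The drop-out shift is 0.06 to 0.20 SD for the baseline gaps tried at 25% loss, and may be zero. The correlation, SD, follow-up numbers and baseline gap are all assumptions.

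The practical weight is small. The outcomes are secondary and descriptive, and the progression criteria use recruitment, retention, engagement and acceptability only. Even paired, the interval per arm would be wide beside the 3-point threshold at moderate correlation. This is a minor improvement worth making because it costs almost nothing.

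**What to change.** In the Data analysis section, state that for WEMWBS, QOLIBRI-OS and BIQS the change from T0 to T1 and from T0 to T2 will be summarised descriptively by arm, in participants with both measurements. Report the mean change, its SD and a paired 95% CI, together with the T0 mean of those same participants.

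Add the number and percent changing by at least 3 points (WEMWBS) and at least 12 points (QOLIBRI-OS), and show baseline scores for completers and non-completers. Keep the visit-wise means as supporting data. The T0–T1 and T0–T2 correlations are an optional extra that would help in planning the definitive trial.

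The cost is one sentence and one table from data already linked by participant, with no new data or participants. The downside is that change is reported on completers only; the baseline comparison makes that limitation visible but does not remove it.
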